### 3.5 Study intervention

The study will compare two schedules of follow-up:

- 1) Standard weekly visits at the outpatient therapeutic feeding center until discharge
- 2) Monthly visits at the outpatient therapeutic feeding center with caregiver support for home-based surveillance, with visits scheduled at weeks 4, 8, 10 and 12 until discharge.

Regardless of intervention assignment, on admission, all children will receive standard medical care as per national guidelines. On admission, caregivers with children admitted to a center randomized to monthly visits will also receive additional instruction and take home materials regarding home-based MUAC and clinical surveillance. All educational materials were developed in consultation with MSF-France, adapted in the field with the LASDEL and pilot tested by Epicentre in Niger in 2014. Draft study materials (provided in Annex 9.1) will be tested and adapted to the study context prior to the start of any study activities in Nigeria.

At all scheduled follow-up visits (either weekly or monthly), children will receive a physical examination and anthropometric assessment. All caregivers will be instructed to return to the health center between scheduled follow up visits if any clinical sign of concern develops.

### 3.6 Random allocation and concealment

The reduced schedule of follow-up will be tested using a stratified cluster randomized design, with the health center as the unit of randomization. All children admitted for outpatient therapeutic feeding at a participating health center will receive the same schedule of follow-up.

Health centers will be stratified by size according to the number of admissions per site in order to promote balance of the intervention among children. Centers within a stratum will be randomized in 1:1 ratio to standard weekly vs. monthly follow-up. Randomization assignment will be made by lottery, in which a local representative will select the name of one of the two interventions from an envelope or opaque jar.

The study will be open, as it will not be possible to blind participants or study staff to frequency of follow up received.

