### 3.4 Target population

The study subjects will be children newly admitted for the treatment of uncomplicated SAM at one of 10 outpatient therapeutic feeding centers.

The specific eligibility criteria for the treatment of uncomplicated SAM:

- age from 6 to 59 months
- MUAC < 115 mm and/or grade 1-2 edema
- Absence of current illness requiring inpatient care\*

\*As per current treatment protocols, children will be referred to inpatient care if presenting with lack of appetite, intractable/continuous vomiting, fever, hypothermia, lower respiratory tract infection, severe respiratory distress, any chest in-drawing, severe anemia (hemoglobin < 7 g/dl), skin infection or lesions requiring IM/IV treatment, altered consciousness, hypoglycaemia, convulsions, severe dehydration, presence of grade 3 edema.

The specific inclusion criteria for the study are:

- Eligible for new admission\*\* at one of the study outpatient therapeutic feeding centers
- Written informed consent of parent or legal guardian

\*\*New admissions include cases of relapse, where the child was previously successfully treated, discharged as cured and returns with a new episode of acute malnutrition within 2 months of discharge. New admission will include children transferred from inpatient care to outpatient care to continue treatment but does not include children transferred from another outpatient site. New admission does not include returned defaulters who were absent for 3 consecutive visits before recovery and return to continue treatment.

The specific exclusion criteria for the study are:

- History of allergy to peanuts
- Any other condition in which, in the judgment of the Field Investigator, would interfere with or serves as a contraindication to protocol adherence or the ability to give informed consent\*\*\*

\*\*\*While determining eligibility, study staff will be asked to use good clinical judgment in considering a participant's overall suitability for inclusion. Some participants may not be appropriate for the study even if they meet all inclusion criteria. For instance, medical,

occupational or other conditions of the participant or parent/guardian may make routine home visits and evaluation difficult or make the child a poor candidate for retention. Any such potential exclusion must be validated by the Field Investigator.

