### 4.3 Evaluation of eligibility

Evaluation of eligibility will occur at the time of first visit/admission to the study outpatient therapeutic feeding centers. Upon arrival, program staff will screen children for eligibility for outpatient treatment as per standard protocol (e.g. age 6 to 59 months; MUAC < 115 mm or grade 1-2 edema; and absence of illness requiring inpatient management). Anthropometry (weight to the nearest 100 g; length (children <24 months) or stature (children ≥ 24 months) to the nearest 0.1 cm; and MUAC to the nearest 0.1 cm using the UNICEF band) will be assessed by program staff using standard techniques described for the WHO Multicenter Growth Reference Study. All study and program staff will be trained and standardized prior to beginning data collection. Standardization sessions will be repeated every 3 months during data collection. Children ineligible for outpatient treatment will not be admitted for nutritional therapy and asked to return home, with explanation of the program admission criteria. These children may be referred to the primary pediatric care program or vaccination program, as needed.

If the child is eligible for outpatient treatment, a study nurse will evaluate the specific study inclusion and exclusion criterion (e.g. new admission, no peanut allergy). If a child presenting to a site assigned to weekly follow-up is eligible for SAM treatment but found ineligible for study inclusion, the child will receive all medical and nutritional treatment with standard weekly follow up at the same site without participating in study data collections. If a child presenting to a site assigned to monthly follow-up is eligible for SAM treatment but does not participate in the study (e.g. parent declines to provide consent or child does not meet inclusion criteria), the child will receive all medical and nutritional treatment with standard weekly follow up at the same site without participating in study data collections. Non-participating children seeking care at sites assigned to monthly follow-up will receive standard care, while all other eligible and participating children included at the monthly site will continue to receive the alternative monthly follow-up as per the random assignment of the site.

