### 5.3 Informed consent

Information about the study aims and procedures will be provided to community leaders in all study villages before recruitment begins. No child will be included as a research participant without documented consent from at least one parent/legal guardian, which must be obtained prior to any study-related procedures are performed. Enrollment into the study will be made voluntarily only after written informed consent. Individual children for whom consent is not provided will not participate in study data collections and will be provided all medical and nutritional treatment with standard follow-up regardless of study assignment (e.g. regardless if the site has, and all other participating children at the site have, been randomized to monthly follow-up).

The informed consent process will give individuals all of the relevant information they need to decide whether to participate and review two documents: a Notice of Information and an Informed Consent Form, both translated into the local language (see Annex 9.3). The informed consent process will begin with a study nurse describing the purpose of the study, procedures and potential risk and benefits of participation to the parent/guardian using the standardized Notice of Information. The study nurse will give the parent/guardian ample opportunity to inquire about details of the study and ask any questions. Illiterate individuals will have the Notice of Information and Informed Consent Form read to them in their native language in the presence of a literate and impartial witness. The witness will sign and date the consent form to attest the consent process appears to be fair and the parent/guardian voluntarily allows the child to be included. The study nurse who administered the consent procedure will sign to confirm that the consent has been obtained following the procedure described in the study protocol. A child will not be enrolled in the study until written informed consent for participation is provided.

One copy of the Informed Consent Form will be kept on file by the Field Investigator for possible inspection by representatives of the ethical committees. The participant's parent/guardian will receive the Notice of Information and a second copy of the signed and dated Informed Consent Form.

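### Section 3.6 conflicts with sections 4.3 and 5.3 on the schedule of non-participating children, and because refusal changes the schedule at monthly sites only, the primary comparison is open to selection bias of unknown direction

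*Protocol*

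**What the plan says.** Three sections of the protocol govern which schedule a child receives.

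- Section 3.6, on allocation: "All children admitted for outpatient therapeutic feeding at a participating health center will receive the same schedule of follow-up".
- Section 4.3, on eligibility: "Non-participating children seeking care at sites assigned to monthly follow-up will receive standard care". The same section spells out what this means at a monthly site: "the child will receive all medical and nutritional treatment with standard weekly follow up at the same site without participating in study data collections". Its examples of non-participation are "parent declines to provide consent or child does not meet inclusion criteria".
- Section 5.3, on consent, says that children without consent "will be provided all medical and nutritional treatment with standard follow-up regardless of study assignment".

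Two other provisions matter. Section 3.4 makes individual consent an inclusion criterion ("Written informed consent of parent or legal guardian"). It also allows exclusion, validated by the Field Investigator, where circumstances would "make the child a poor candidate for retention". Section 3.6 adds: "The study will be open, as it will not be possible to blind participants or study staff to frequency of follow up received".

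Section 3.7 assumes recovery of 0.80 with weekly visits and a non-inferiority margin of -0.05. Section 3.9 compares recovery by generalized estimating equations under the intention-to-treat principle.

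**The concern.** The wording conflict is plain: a center cannot give every admitted child the same schedule and also give some of them a different one.

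The larger matter is what the rule in 4.3 and 5.3 does to enrolment. The schedule of each center is known before any caregiver is asked for consent. At a weekly site, a child who is not enrolled still attends weekly. At a monthly site, a child who is not enrolled moves to weekly visits. The consequence of refusing, or of being excluded at staff discretion, therefore depends on the arm. Children who are not enrolled leave the study data, so the analysis sees only those who remain.

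If the children who remain differ in prognosis between arms, the estimated difference in recovery mixes the effect of the schedule with the effect of who enrolled. Randomizing centers does not protect against selection that happens after allocation is known. With a 5-point margin, a shift of one or two points is enough to matter.

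**Working it through.** **Step 1. Schedule by site and participation, under 4.3 and 5.3.**

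| Site | Enrolled | Not enrolled | Does non-enrolment change the schedule? |
|---|---|---|---|
| Weekly | weekly, analysed | weekly, not analysed | no |
| Monthly | monthly, analysed | weekly, not analysed | yes |

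Section 3.6, read literally, would put monthly in the lower right schedule cell. Reading it as covering enrolled children only removes the wording conflict, but the asymmetry in the last column stays.

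**Step 2. Reproduce the plan's own precision.** Inputs from 3.7: recovery 0.80 in both groups, margin 0.05, one-sided 0.05, intraclass correlation 0.002, 350 children per center. From 3.1: 10 centers allocated 1:1, so 5 per arm.

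- Design effect: 1 + (350 - 1) × 0.002 = 1.698.
- Children per arm: 5 × 350 = 1750.
- Standard error: √(2 × 0.80 × 0.20 × 1.698 / 1750) = 0.0176.
- Power: Φ(0.05 / 0.0176 - 1.645) = 0.88, the stated figure. The score-test version gives 0.883.

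**Step 3. Shift in observed monthly recovery.** Let f be the share of eligible children not enrolled at monthly sites and r the recovery they would have had. Neither is in the protocol, so both are assumptions.

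Shift = (0.80 - f × r) / (1 - f) - 0.80 = f × (0.80 - r) / (1 - f)

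Example: f = 0.10 and r = 0.60 give 0.10 × 0.20 / 0.90 = +0.022.

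| f | r = 0.60 | r = 0.70 | r = 0.80 | r = 0.90 |
|---|---|---|---|---|
| 5% | +1.1 | +0.5 | 0 | -0.5 |
| 10% | +2.2 | +1.1 | 0 | -1.1 |
| 20% | +5.0 | +2.5 | 0 | -2.5 |

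Entries are percentage points and assume no net selection at weekly sites.

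**Step 4. Net bias is a difference between arms.** Weekly sites can lose children too. If 10% are lost at monthly sites and 5% at weekly sites, both with r = 0.70, the net bias is 0.10 × 0.10 / 0.90 - 0.05 × 0.10 / 0.95 = 0.0111 - 0.0053 = +0.6 points. If f and r are the same in both arms, it is zero.

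**Step 5. What a net bias b does to the test.**

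- Upward bias: at a true difference of -0.05 the standard error is √((0.80 × 0.20 + 0.75 × 0.25) × 1.698 / 1750) = 0.0184. The false non-inferiority rate is Φ(b / 0.0184 - 1.645), about 14% for b = 0.01 and 29% for b = 0.02, against a nominal 5%. With 280 analysed per center (350 less the 20% loss) it is 13% and 27%.
- Downward bias: with no true difference and b = -0.011, power is Φ((0.05 - 0.011) / 0.0176 - 1.645) = 0.71, against 0.88.

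**The case against.** The best defense is that section 4.3 sets out the working rule in full and 5.3 repeats it for refusals. Site staff would follow those sections, and the sentence in 3.6 is only a summary. That stands as far as operations go, and on wording alone the correction is editorial. It does not remove the arm-dependent consequence of refusal.

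A reader might infer that caregivers of sicker children will decline at monthly sites, so that the bias favors non-inferiority. No passage supports that, and several features weaken it or pull the other way:

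- Section 1.1 expects monthly visits to lower caregivers' opportunity cost, which could draw in families who are hard to retain.
- Sections 3.5 and 4.6 tell caregivers to return between visits if a sign of concern appears, which weakens the motive to refuse.
- Sections 3.4 and 4.10 send children who need inpatient care elsewhere before enrolment, which narrows the range of severity.
- Section 4.1 plans community engagement to support high participation.

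A reader might also infer that the weekly arm is close to unselected. The documents do not show this: weekly sites apply the same consent and exclusion rules and lose refusers from the data in the same way. Nor is this crossover among analysed children, because non-participants are not analysed.

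Finally, covariate lists and reporting of enrolment flow are commonly left to the statistical analysis plan, which is not shown. Their absence from 3.9 is therefore not itself an error. Counts of refusals are different in one respect: they must be recorded during recruitment. The protocol text describes no such log, although the annexed case report forms, which were not available, may contain one.

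**Conclusion.** The point holds in two parts. First, 3.6 contradicts 4.3 and 5.3, and the passages must be reconciled. Second, open allocation of centers followed by child-level consent, with a consequence of refusal that differs by arm, leaves the primary non-inferiority comparison open to selection bias. Intention-to-treat among enrolled children does not repair it.

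Direction and size are unknown. Ten percent non-enrolment at monthly sites would move observed monthly recovery by between +2.2 and -1.1 points. This rests on assumed would-be recovery of 0.60 to 0.90, overall recovery of 0.80 and no net selection at weekly sites. An upward shift makes a false claim of non-inferiority more likely, and a downward shift costs power. The documents do not support saying that the bias will occur or that it will favor monthly visits. They do support recording what is needed to judge it.

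**What to change.** 1. Reconcile section 3.6 with 4.3 and 5.3 so that the protocol states one rule for the schedule of non-participating children. Which rule stands is for the sponsor to decide.
2. During recruitment, keep a log by site and arm of children who are eligible, who refuse, and who are excluded, with the reason for exclusion.
3. In 3.9, adjust the recovery comparison for a short pre-specified list of child-level admission variables: MUAC, edema, age and transfer from inpatient care. All are known at admission. Keep the effect on the risk-difference scale of the -0.05 margin, by an identity link or by standardisation, because an odds ratio could not be set against that margin.
4. State in advance that the non-inferiority conclusion will be qualified if participation differs by arm.

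The cost is a wording change, a simple tally at 10 centers and a little more analysis. The covariate list must stay short with 10 clusters. Adjustment cannot remove selection on unmeasured factors, such as caregiver concern, so the log is needed even if the model is adjusted.

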### 3.7 Power calculations

Ten outpatient therapeutic feeding centers in this setting can be expected to admit total of 3,500 children for the treatment of uncomplicated SAM over 12 months (3,777 children admitted at 10 facilities in 2016). Assuming a baseline risk of nutritional recovery in the weekly

follow-up group of 0.80, intraclass correlation of 0.002 and significance level of 0.05 using the one-sided Score test, and allowing for 20% loss to follow up, a sample size of 350 children per health facility (2100 per group) will achieve 88% power to detect a non-inferiority margin difference between the group proportions of -0.05.

|                        | Difference in recovery between weekly vs. monthly follow up groups (n = 350 per site) |                  |                  |
|------------------------|---------------------------------------------------------------------------------------|------------------|------------------|
| Intraclass correlation | $\Delta = -0.15$                                                                      | $\Delta = -0.10$ | $\Delta = -0.05$ |
| 0.001                  | 1.00                                                                                  | 1.00             | 0.94             |
| 0.002                  | 1.00                                                                                  | 1.00             | 0.88             |
| 0.01                   | 1.00                                                                                  | 0.97             | 0.54             |

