### 3.0 METHODOLOGY

#### 3.1 Study design

This study will be conducted as a stratified cluster randomized trial of a monthly schedule of follow up in the treatment of uncomplicated SAM among children aged 6 to 59 months. The unit of randomization will be the outpatient therapeutic feeding center. The 10 health centers supported by UNICEF will be stratified by size ( $\pm 500$  admissions per site), and centers within a stratum will be randomized in a 1:1 ratio to one of two schedules of treatment: (1) standard weekly visits or (2) monthly visits with support for home-based surveillance.

Distribution of the therapeutic feeding rations, as well as medical and anthropometric surveillance, will take place on a weekly or monthly basis until discharge according to the random assignment of the site. Caregivers in the monthly visit group will receive additional instruction at admission regarding home-based MUAC measurement and clinical surveillance.

Regardless of intervention assignment, all children with uncomplicated SAM will receive standard medical care on admission as per national guidelines, and a home visit 3 months following discharge from the nutritional program. Additional data collection, including coverage assessment and economic costing analysis will be used to address the secondary objectives related to the evaluation of coverage and cost-effectiveness, respectively.

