### 3.9 Statistical analysis

The primary outcome is nutritional recovery. Secondary outcomes include hospitalization, average daily weight gain among recovered children, defaulting, and relapse within 3 months.

All analyses will use the intention-to-treat principle and account for the stratified cluster design. We will use generalized estimating equations and robust standard errors to compare the proportion of children recovered, hospitalized, defaulted or relapsed within 3 months, and mixed effects models to compare average daily weight gain.

Interim analysis at 6 months of inclusion will be conducted to ensure the safety of children included. No adjustment will be made for multiple testing. All P values will be 2-sided, with  $P < 0.05$  considered statistically significant. Analyses will be performed using SAS version 9.3 or higher (SAS Institute Inc., Cary, NC).

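### The 88% power in section 3.7 uses a large-sample normal test; with 10 randomized centers, a cluster-level test that holds one-sided 0.05 has about 82–83% power at the same inputs

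*Protocol*

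**What the plan says.** Section 3.7 takes 0.80 as the recovery proportion under weekly visits and bases its power on "intraclass correlation of 0.002 and significance level of 0.05 using the one-sided Score test". After mentioning an allowance of 20% for loss, it states that "a sample size of 350 children per health facility (2100 per group) will achieve 88% power". The margin behind that figure is a recovery difference of -0.05. A table then gives power for 350 per site at three ICCs and three margins. The -0.05 column reads 0.94, 0.88 and 0.54 for ICC 0.001, 0.002 and 0.01.

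Section 3.1 fixes the number of randomized units at 10 centers, stratified by size at 500 admissions: "centers within a stratum will be randomized in a 1:1 ratio to one of two schedules of treatment". That is about 5 centers per arm.

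Section 3.9 states: "All analyses will use the intention-to-treat principle and account for the stratified cluster design". For recovery it plans GEE with robust standard errors. Section 3.7 makes no allowance for the small number of clusters or for centers of different size.

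**The concern.** A score test with a normal critical value, inflated by a design effect, treats the between-center variance as known. That is a reasonable approximation with many clusters. With 5 per arm the variance must be estimated from a handful of centers, so a test that keeps its level needs a larger critical value and has less power than the normal formula gives.

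At stake is the stated chance of success for the primary non-inferiority comparison. If the two schedules are truly equal, the protocol implies about a 12% chance of failing to show non-inferiority. The question is whether the design can deliver that at the level it states.

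**Working it through.** **Inputs.** From section 3.7: recovery 0.80 (true difference taken as 0), margin -0.05, one-sided 0.05, ICC 0.001, 0.002 or 0.01, and m = 350 per center. From section 3.1: 10 centers randomized 1:1, so k = 5 per arm.

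**Step 1: reproduce the protocol's figure.**

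- Design effect: DE = 1 + (m − 1) × ICC = 1 + 349 × 0.002 = 1.698.
- Standard error of the difference: √(2 × 0.8 × 0.2 × 1.698 / (5 × 350)) = 0.01762.
- Standardized margin: 0.05 / 0.01762 = 2.838.
- Normal power: Φ(2.838 − 1.645) = 0.884. The Farrington-Manning restricted variance gives 0.883. The protocol prints 0.88.

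The same steps reproduce all nine printed cells. The match requires a normal reference, equal centers and 350 analysed per center, with no loss taken off.

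**Step 2: use the reference distribution that 10 centers allow.** The standard error is unchanged. The test statistic is referred to t with 10 − 2 = 8 degrees of freedom (critical value 1.860). If a two-level size stratum is fitted, there are 7 (critical value 1.895). Power is the upper tail of the noncentral t, with the standardized margin as noncentrality.

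| ICC, margin | DE | Margin / SE | Printed | Normal | t, 8 df | t, 7 df |
|---|---|---|---|---|---|---|
| 0.001, -0.05 | 1.349 | 3.184 | 0.94 | 0.938 | 0.895 | 0.887 |
| 0.002, -0.05 | 1.698 | 2.838 | 0.88 | 0.884 | 0.827 | 0.817 |
| 0.01, -0.05 | 4.490 | 1.745 | 0.54 | 0.540 | 0.480 | 0.472 |
| 0.01, -0.10 | 4.490 | 3.490 | 0.97 | 0.967 | 0.937 | 0.931 |

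The other five cells stay at about 1.00.

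**Step 3: check by simulation.** In 200,000 trials with beta-binomial centers of 350, ICC 0.002 and a center-level t-test, power was 0.826 with the 8-df critical value and 0.818 with the 7-df one. Error at the margin was 0.050 and 0.047.

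**Step 4: check whether the planned analysis restores 88%.** With equal centers and 5 per arm, an uncorrected robust variance averages 4/5 of the unbiased one. The effective critical value on the t scale is then 1.645 × √0.8 = 1.471. On 8 df this gives power 0.908, but a one-sided error of 0.090 (simulated 0.907 and 0.089). The higher power comes from exceeding the stated 5% level.

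**Step 5: check the number analysed.** At ICC 0.002:

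- If 350 is enrolled and 20% are lost, 280 are analysed per center. DE = 1.558 and margin / SE = 2.650. Power is 0.842 (normal), 0.780 (8 df) or 0.770 (7 df).
- If the 2,100 per group means 420 enrolled per center, 336 are analysed (0.8 × 420). Power is 0.877 (normal), 0.819 (8 df) or 0.809 (7 df).

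Under either reading, the t reference lowers power by about 6 to 7 points.

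**The case against.** **The arithmetic is not wrong.** This stands. The protocol names its test, and its figures are correct for that test. A reader might infer a calculation slip, but the table reproduces exactly. The fault is an approximation that does not suit 10 clusters.

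**The 82–83% belongs to a test the protocol does not name.** This stands as a condition. Section 3.9 states neither a t reference nor degrees of freedom, and a small-sample correction is commonly left to the SAP, so its absence here is no finding. The restated power holds if the primary analysis uses a small-sample-valid test. It would be too strong to say the result is independent of how the standard error is handled. But neither route supports 88% at 5%: without correction the level is exceeded, and with correction power returns to about 82%.

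**Seven degrees of freedom charge for the stratum but give no credit for it.** This also stands. If stratifying reduced the residual ICC from 0.002 to about 0.0011, 7-df power would be about 0.88. The protocol gives no basis for any such reduction. It also does not say how many strata there are beyond the cut at 500 admissions. So 0.82 is not preferable to 0.83, and the range is reported.

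**Unequal size.** A reader might want a definite further loss. Stratifying by size implies that sizes differ, but the protocol gives only a 2016 total (3,777 at 10 facilities) and a uniform 350. The direction is clear; the amount is not.

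**The shift is small.** Six points is modest beside the table's own spread of 0.94 to 0.54 across ICCs, and an inconclusive result would be read mainly from its confidence interval. That limits the importance of the point, but the printed figure remains too high.

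**Conclusion.** The point holds in this form. At the protocol's own inputs, with 350 analysed children in each of 10 equal centers, a cluster-level test that holds one-sided 0.05 has about 82–83% power against the -0.05 margin at ICC 0.002, not 88%. The chance of missing non-inferiority when the schedules are equal is about 17–18% rather than 12%, roughly half as large again.

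This assumes a small-sample-valid primary test on 7 or 8 between-center degrees of freedom, equal center sizes, no loss, and no variance removed by stratification.

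A reader might go on to infer that the trial is underpowered or needs more centers. The documents do not support that: 82–83% is still above 80%. The lower 77–78% applies only if 280 per center are analysed, which section 3.7 leaves unclear.

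**What to change.** In section 3.7:

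- Recompute the power and every table cell with a t reference on the between-center degrees of freedom. At 350 analysed and equal sizes, the -0.05 column becomes about 0.89–0.90, 0.82–0.83 and 0.47–0.48, and the ICC 0.01 / -0.10 cell about 0.93–0.94.
- Name the test and significance level the power refers to, so that the primary analysis can be matched to it. Section 3.9 makes all P values two-sided; at 0.025 per side the ICC 0.002 figure with 350 analysed would be 68–70%.
- State whether 350 is enrolled or analysed, and reconcile it with 2,100 per group (5 × 350 = 1,750). If 280 are analysed, the cell is about 0.77–0.78.
- If 2016 admissions by facility are available, replace the design effect with 1 + ((1 + CV²) × m − 1) × ICC, where CV is the coefficient of variation of center size and m its mean.

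The cost is rewording one paragraph and one table. No extra children or centers are needed. The stated power falls by about 6 points at ICC 0.002, before any allowance for unequal sizes or loss.
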